**Screening Phase**

A brief telephone pre-screening is performed before the screening visit to avoid unnecessary visits for patients. This is conducted following verbal permission to access medical records and a verbal consent to a short pre-screening assessment to determine whether participants may qualify for full screening. Screening includes psychiatric and medical history, inclusion/exclusion criteria assessment, safety blood tests (glucose, liver, kidney), and, when clinically indicated additional laboratory tests to exclude common medical conditions and support eligibility assessment, ECG, informed consent (with a 2-week consideration period), pregnancy test and urine toxicology (U-tox). The time from screening to the first psilocybin dosing session must not exceed 8 weeks.

**Preparation Phase**

- Preparation Session 1 & Baseline Assessment (Week 0): Psychoeducation about psilocybin, breathing and relaxation techniques, rapport-building with therapists, and discussion of expectations and concerns.
  Includes full baseline assessments (list provided as attachment to protocol:
  - Expectation of Treatment Scale (ETS-BF)
  - Readiness and Motivation Questionnaire (RMQ)
  - General Change Mechanisms Questionnaire (GCMQ)
  - Patient Health Questionnaire (PHQ-9)
  - Generalized Anxiety Disorder scale (GAD-7)
  - Eating Disorder Examination Questionnaire (EDE-Q )
  - Columbia-Suicide Severity Rating Scale (C-SSRS)
  - Brief Psychiatric Rating Scale – Extended (BPRS+)
  - Satisfaction With Life Scale (SWLS)
  - Positive and Negative Affect Schedule (PANAS)
  - Harmony in Life Scale (HILS)
  - Ten Item Personality Inventory (TIPI)
  - Honesty-Humility Scale (HH)EGON
- Visual size estimation (EGON)

Vital signs, ECG, blood glucose, urine drug screening, pregnancy test, fMRI, BMI and blood sampling for BDNF and safety labs are also conducted.

Preparation Session 2 (Week 1): Conducted 7–10 days after Preparation 1, and 2–3 days before psilocybin dosing.

**Dosing and Integration Phase**

Dosing Session 1 (Week 1): Psilocybin 25 mg under therapeutic support with ECG, blood glucose and blood pressure/pulse monitoring.

Integration Session 1 (Day after Dosing 1): Reflection, fMRI, blood sampling (including glucose, liver, kidney, BDNF), and reassessments with RMQ, GCMQ, PHQ-9, GAD-7, C-SSRS, BPRS+, SWLS, PANAS, HILS, TIPI, ECG and blood pressure/pulse. Psychedelic Experience related scales; Altered States of Consciousness Rating Scale (5D-ASC), Mystical Experience Questionnaire (MEQ-4), Meaningful Life Experience Rating (MLE).

Integration Session 2 (Week 2): Continued psychological integration support.

Integration Session 3 (Week 3): Summary of first dosing experience and preparation for second dosing. A pregnancy test is performed.

Dosing Session 2 (Week 4): Second psilocybin 25 mg administration under identical conditions as first dosing session.

Integration Session 4 (Day after Dosing 2): Reflection, blood sampling (including glucose, liver, kidney, BDNF), and reassessments with RMQ, GCMQ, PHQ-9, GAD-7, C-SSRS, BPRS+, SWLS, PANAS, HILS, TIPI, ECG and blood pressure/pulse. Psychedelic Experience related scales; Altered States of Consciousness Rating Scale (5D-ASC), Mystical Experience Questionnaire (MEQ-4), Meaningful Life Experience Rating (MLE).

Integration Session 5 (Week 5): Final integration session and preparation for long-term follow-up.

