Aim: To explore the safety, tolerability, and initial efficacy of psilocybin administered with psychological support compared to Treatment as Usual (TAU) in adolescents and young adults aged 16-35 with anorexia nervosa (AN).

Primary Objective: To assess the safety and tolerability of psilocybin 25 mg in this population.

Secondary Objectives: To evaluate the efficacy of psilocybin with psychological support in reducing AN symptom compared to TAU, investigate potential mechanisms of action through self-report questionnaires, neuroimaging and BDNF analysis, and conduct qualitative analysis of subjective experiences.

Trial Design: Open, randomized controlled trial with two arms: (1) two doses of psilocybin (25 mg) with psychological support with one month apart and alongside treatment as usual, and (2) Treatment as Usual (TAU).

Trial Population: Adolescents and young adults aged 16-35 diagnosed with anorexia nervosa.

Number of Subjects: 40 participants (20 per group).

Inclusion Criteria: Diagnosed with AN per DSM-5, aged 16-35, BMI >16, who have experienced at least one period of weight gain followed by weight loss.

Exclusion Criteria: Psychosis, bipolar disorder, substance use disorder, contraindicated medications, severe medical conditions, or metal contraindications for MRI.

Intervention: Two doses of 25 mg psilocybin with psychological support, or TAU. Psilocybin sessions will be accompanied by preparatory and integration sessions.

Investigational Medicinal Product Dosage Administration: Psilocybin 25 mg administered orally during supervised sessions.

Ethical Considerations/Benefit-Risk: Comprehensive safety monitoring, support during sessions, and procedures in place for managing any adverse events. First 25 participants included above 18 years of age, followed by 15 patients between 16-17 years of age. Safety review committee after first 10 psilocybin dosing sessions to review adverse events and protocol adherence. Literature on psilocybin clinical trials report low risk for adverse events and large gap in treatment options for patients with relapse in anorexia nervosa.

Planned Duration of the Trial: Q3 2025 – Q2 2027.

2. Background and Rationale

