This pilot study will assess the safety, tolerability, and preliminary efficacy of administering 25 mg of psilocybin, spaced one month apart, in combination with treatment as usual (TAU) for adolescents and young adults aged 16-35 with AN. The study will compare this combined approach to the effects of TAU alone. Additionally, it will explore potential mechanisms of action through self-reports, neurobiological assessments, and neuroimaging techniques.

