**Rationale for dosing interval:**

Several clinical trials have consistently demonstrated that administering two doses of psilocybin spaced 2 to 4 weeks apart is both safe and therapeutically appropriate when delivered under professional supervision with structured integration support (Bogenschutz et al., 2022; Carhart-Harris et al., 2021; Davis et al., 2021; Garcia-Romeu et al., 2015; Gukasyan et al., 2022). These dosing intervals are grounded in empirical findings from multiple populations and indications. For instance, Carhart-Harris et al. (2021) administered two 25 mg doses of psilocybin three weeks apart to 59 individuals with depression, reporting no serious adverse events (SAEs) and only transient effects such as headache and nausea. Garcia-Romeu et al. (2015) conducted a feasibility study in 15 smokers, administering 20 mg/70 kg and 30 mg/70 kg doses spaced by approximately two weeks; again, no SAEs were reported, and the design highlighted psychological integration. Davis et al. (2021) employed a two-week interval between doses in 24 patients with depression. Finally, Bogenschutz et al. (2022) studied 93 individuals with alcohol use disorder, spacing two 25 mg doses four weeks apart, with no serious adverse drug reactions noted. Collectively, these studies support the 4 week interval as an evidence-based standard that balances therapeutic efficacy with participant safety.

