5.3 Biological Sampling Procedures

Blood samples (up to 5 ml per participant per occasion) will be collected for the analysis of Brain-Derived Neurotrophic Factor (BDNF) as an exploratory biomarker and for tolerance and safety measurements. Additionally, we aim to collect one tube (5 ml = 10ml in total) of additional whole blood per occasion for future analysis.

BDNF samples will be taken at five key time points: (1) before treatment (baseline), (2) and (3) at first integration session after Psilocybin 25mg dosing, (4) at 5 weeks, and (5) during the 6-month follow-up. This ensures comprehensive longitudinal data collection.

Blood samples of glucose, kidney and liver status will be measured for safety and tolerance reasons. None of these blood samples are collected or stored.

All blood samples are done by a standard peripheral venous sampling method performed by a nurse at the research facility at the university hospital clinic for psychiatry at [name].

Procedures will be implemented to minimize discomfort during blood collection, such as using pediatric needles for younger participants when necessary. Blood collection and processing will follow standardized protocols to ensure sample integrity.

Handling, Storage, and Destruction of Biological Samples:

Blood samples taken for analysis of BDNF will be analyzed at the Wallenberg Neuroscience Center or Avdelningen för neurokemi, thereafter stored at Region Skåne Bio bank for maximum 10 years under secure conditions and in accordance with Swedish regulations and the protocol for “Följsamhet med regler för hantering av biologiska prov”.

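### The visit schedule implies about three weeks between the two psilocybin doses, while the synopsis, the study summary and the rationale's conclusion give one month or four weeks

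*Protocol*

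**What the plan says.** The Protocol gives the dose-to-dose interval in words in three places:

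- The synopsis (Trial Design) describes "two doses of psilocybin (25 mg) with psychological support with one month apart and alongside treatment as usual".
- The study summary that opens section 2 repeats the one-month spacing.
- The dosing-interval rationale in section 5.1 reviews trials with intervals of about two, three and four weeks, describes the range of two to four weeks as appropriate, and ends: "Collectively, these studies support the 4 week interval as an evidence-based standard".

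The visit schedule in section 5.2 gives the timing by week label and never states the interval itself. Preparation 1 is the baseline visit at Week 0. Preparation 2, labelled Week 1, is "Conducted 7–10 days after Preparation 1, and 2–3 days before psilocybin dosing". Then come "Dosing Session 1 (Week 1): Psilocybin 25 mg under therapeutic support" and, after integration sessions at Weeks 2 and 3, "Dosing Session 2 (Week 4): Second psilocybin 25 mg administration under identical conditions as first dosing session". No visit window is given for the second dose. Integration Session 5 follows at Week 5 and the main outcome visit at Week 9.

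Section 5.3 lists the last two BDNF samples as "4) at 5 weeks, and (5) during the 6-month follow-up". Section 8.1 also gives five weeks as a time for measuring BMI. Neither section says what the five weeks are counted from.

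**The concern.** The primary objective is the safety and tolerability of psilocybin 25 mg, given here as a two-dose regimen. The time between doses is part of what defines that regimen, and the Protocol states it in two ways that do not agree. A team that books visits from section 5.2 departs from the synopsis, the study summary and the rationale's conclusion. A team that keeps four weeks departs from section 5.2. Participants could be treated at different intervals with no rule for saying which of them followed the Protocol, yet the interim review in section 10.5 is asked to judge protocol adherence.

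There is also a measurement consequence. Week 9 carries the fMRI, BDNF, EDE-Q and BMI assessments, and its distance from the second dose depends on which statement is followed.

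**Working it through.** **Inputs, all from the Protocol**

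- Baseline (Preparation 1): Week 0, taken as day 0 (section 5.2).
- Preparation 2: 7 to 10 days after Preparation 1 (section 5.2).
- First dose: 2 to 3 days after Preparation 2, labelled Week 1 (section 5.2).
- Second dose: labelled Week 4, with no window (section 5.2).
- Stated interval: one month (synopsis, section 2); four weeks, i.e. 28 days (conclusion of the section 5.1 rationale).

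**Step 1. Day of the first dose.** Earliest 7 + 2 = day 9; latest 10 + 3 = day 13.

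**Step 2. Meaning of the week labels.** The Protocol does not define them. If Week k covers days 7k to 7k + 6, Week 1 is days 7 to 13 and the first dose always falls inside it. This is the only convention tried that agrees with the Week 1 label on the first dose. Week 4 is then days 28 to 34.

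**Step 3. Interval on that convention.** Shortest 28 − 13 = 15 days; longest 34 − 9 = 25 days.

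**Step 4. Other conventions.**

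| Reading of Week 4 | Second dose, day | Interval, first dose on day 9–13 |
|---|---|---|
| Days 7k to 7k + 6 | 28–34 | 15–25 days |
| Nominal day 7k | 28 | 15–19 days |
| Days 7(k − 1) + 1 to 7k | 22–28 | 9–19 days |
| Day 7k ± 3 | 25–31 | 12–22 days |

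Ignoring the preparation windows and using the labels alone, Week 1 to Week 4 is nominally 3 × 7 = 21 days, and at most 34 − 7 = 27 days. The stated 28 days or one month is not reproduced on any of these readings.

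**Step 5. Size of the gap.** Against 28 days, the nominal shortfall is 28 − 21 = 7 days. On the step 3 range it is 28 − 25 = 3 to 28 − 15 = 13 days.

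**Step 6. Where a 28-day interval would fall.** 9 + 28 = day 37 to 13 + 28 = day 41. On the step 2 convention this is Week 5 (days 35 to 41), the week already assigned to Integration Session 5.

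**Step 7. Distance from the second dose to Week 9** (days 63 to 69).

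- Schedule as written, second dose on day 28–34: 63 − 34 = 29 to 69 − 28 = 41 days.
- Doses 28 days apart, Week 9 unchanged: 63 − 41 = 22 to 69 − 37 = 32 days.

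**Step 8. The five-week time point.** The Week 5 visit in section 5.2 lists neither BDNF nor BMI; Week 9 lists both. Counted from a second dose at Week 4, five weeks gives 4 + 5 = Week 9 and the sections agree. Counted from baseline, it is Week 5 and they do not.

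**The case against.** A reader might infer that the regimen to be tested is not the one the Protocol justifies. The text does not support that. The rationale that ends on four weeks also describes two to four weeks as appropriate and cites a trial of two 25 mg doses three weeks apart. An interval of 15 to 25 days (15/7 = 2.1 to 25/7 = 3.6 weeks) lies inside that range. What the schedule misses is the specific interval on which the rationale, the synopsis and the summary settle. Nor does the Protocol say that section 5.2 takes precedence over the synopsis.

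The range of 15 to 25 days rests on reading Week 4 as a seven-day block, which the text does not state. A visit window of a few days could also close the gap at one end: day 9 plus 28 is day 37, three days beyond day 34. Section 8.2 refers to an attached Schedule of Assessments that is not at hand and may contain windows. These points limit the precision of the range. They do not remove the contradiction, because the nominal labels are three weeks apart and an attachment could agree with only one of the two statements in the body.

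It is also tempting to say that the five-week BDNF sample could be drawn before the second dose. That needs both a hypothetical 28-day interval and a count from baseline, which the text does not state. Section 5.3 lists this sample after the post-dosing ones, which points the other way. Only the missing origin stands as a point.

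Finally, the primary endpoint is the incidence of adverse events, collected from the first dose to 12 months, and no change to its analysis has been shown. The effect shown is on the definition of the regimen and on the timing of the Week 9 assessments.

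**Conclusion.** The contradiction is real. Section 5.2 implies about three weeks between doses: nominally 21 days, or 15 to 25 days if Week 4 means days 28 to 34. Every week convention tried gives less than 28 days. The synopsis and study summary give one month, and the rationale concludes on four weeks. The finding itself does not depend on the seven-day reading of Week 4; the exact range does.

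Following one statement or the other shifts the Week 9 assessment from 29–41 days to 22–32 days after the second dose, assuming Week 9 stays fixed to baseline. The undefined five-week time point is a secondary ambiguity. Because the interval is part of the regimen whose safety is the primary objective, the passages should be brought into agreement before dosing. Nothing here bears on which interval is clinically preferable.

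**What to change.** Reconcile the synopsis, the study summary in section 2, the dosing-interval rationale in section 5.1 and the schedule in section 5.2 to a single dose-to-dose interval. State it in days from the first dose, with a visit window for the second. Then check that the Week 5 and Week 9 visits remain consistent with it. In sections 5.3 and 8.1, say what the five weeks are counted from and match this to the visit list, which places BDNF and BMI at Week 9. If the attached Schedule of Assessments gives timings, align it in the same step. The choice of interval belongs to the sponsor's clinicians.

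The cost is a text amendment to the Protocol, with no added visits or participants.

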**Primary Endpoint Week 9**

Includes full safety and outcome evaluations:
- fMRI

- blood sampling (including glucose, liver, kidney, glucose, BDNF)
- Vital signs, ECG, U-tox

- BMI
- AE/SAE monitoring
- Readiness and Motivation Questionnaire (RMQ)
- General Change Mechanisms Questionnaire (GCMQ)
- Patient Health Questionnaire (PHQ-9)
- Generalized Anxiety Disorder scale (GAD-7)
- Eating Disorder Examination Questionnaire (EDE-Q)
- Columbia-Suicide Severity Rating Scale (C-SSRS)
- Brief Psychiatric Rating Scale – Extended (BPRS+)
- Satisfaction With Life Scale (SWLS)
- Positive and Negative Affect Schedule (PANAS)
- Harmony in Life Scale (HILS)
- Ten Item Personality Inventory (TIPI)
- Honesty-Humility Scale (HH)

- Visual size estimation (EGON)

**Intensive Follow-Up Phase Month 3,4 and 5**

Follow-up visits include:
- Eating Disorder Examination Questionnaire (EDE-Q)
- Columbia-Suicide Severity Rating Scale (C-SSRS)
- Brief Psychiatric Rating Scale – Extended (BPRS+)
- AE/SAE monitoring
- BMI, blood pressure, ECG
- Glucose, U-tox

**6-Month Follow-Up**

Same as primary endpoint assessments (except not fMRI), including:

- blood sampling (including glucose, liver, kidney, BDNF)
- Vital signs, ECG, U-tox

- BMI
- AE/SAE monitoring
- Readiness and Motivation Questionnaire (RMQ)
- General Change Mechanisms Questionnaire (GCMQ)
- Patient Health Questionnaire (PHQ-9)
- Generalized Anxiety Disorder scale (GAD-7)
- Eating Disorder Examination Questionnaire (EDE-Q )
- Columbia-Suicide Severity Rating Scale (C-SSRS)
- Brief Psychiatric Rating Scale – Extended (BPRS+)
- Satisfaction With Life Scale (SWLS)
- Positive and Negative Affect Schedule (PANAS)
- Harmony in Life Scale (HILS)
- Ten Item Personality Inventory (TIPI)
- Honesty-Humility Scale (HH)

- Visual size estimation (EGON)

**Extended Follow-Up Phase**

9-Month Follow-Up

- Eating Disorder Examination Questionnaire (EDE-Q)
- Columbia-Suicide Severity Rating Scale (C-SSRS)
- Brief Psychiatric Rating Scale – Extended (BPRS+)
- AE/SAE monitoring
- BMI, blood pressure, ECG
- glucose, U-tox

12-Month Final Follow-Up
- Eating Disorder Examination Questionnaire (EDE-Q)
- Columbia-Suicide Severity Rating Scale (C-SSRS)
- Brief Psychiatric Rating Scale – Extended (BPRS+)

- Patient Health Questionnaire (PHQ-9)
- Generalized Anxiety Disorder scale (GAD-7)

- Ten Item Personality Inventory (TIPI)

- Meaningful Life Experience Rating (MLE).
- AE/SAE monitoring
- BMI, blood pressure, ECG
- glucose, U-tox

Participants who show signs of psychological or physical deterioration at any point during the study between follow-ups are instructed to contact the research team at any time and will be offered additional assessment and support.

***Description of Psilocybin Administration and Psychological support***

Psychological support includes a non-directive preparation and integration pre- and post-dosing sessions according to protocol manual, alongside support for the patient on the dosing session day. The study follows the guidelines for safe research with psychedelics (Johnson et al, 2008).

Preparation session

Standard preparation in psilocybin clinical trials including psychoeducation of the effects of psilocybin, breathing techniques, getting to know the two therapists (at least one licensed health care professionals experienced with eating disorders and trained in psilocybin therapy including either a psychologists, psychiatrists, nurse and physiotherapist, ) , one male and one female), the onsite psychiatrist on call during dosing session, and other relevant professionals of the research team, practicing how to manage challenging episodes of the dosing session, agreeing on contracts for touch and being able to ask questions. A standardized preparation script will ensure consistency across participants. The assistant therapist can be non-licensed healthcare personnel experienced with the anorexia nervosa population, such as a healthcare assistant. All psychological support therapists must have done all specific 5-day training in the psiAN manual.

Dosing session day

The dosing session, lasting 6-8 hours, is supported by the lead and assisting therapists introduced during preparation sessions. The psilocybin's acute effects persist for 4-6 hours, recorded via video and audio. Participants, lie down with an optional eye mask, experience the session in a comfortable room with a pre-selected music playlist, respecting individual preferences.

Therapists provide support and guidance if requested but with minimal psychotherapeutic focus.

Therapists will follow pre-established protocols for de-escalation and grounding in case of distressing experiences.

Parents are introduced at the session's end with participant approval.

During the dosing session, a medically trained study doctor will be available, equipped for emergencies in the unlikely event of serious adverse events related to psilocybin risks.

Integration session

The participant will be back at the research facility two times after each dosing session for integration sessions (approx. 1-2 hours) with the therapists to further explore the dosing session and its effects.

Integration sessions will include structured discussions about insights gained, with therapists facilitating connections between the experience and the participant’s therapeutic goals.

**Monitoring Post-Psilocybin Administration adverse events between visits.**

Participants who experience significant psychological distress, abnormal vital signs, or other health concerns between study visits are instructed to contact the research team during daytime hours using the contact details provided in the participant information sheet. During evenings or weekends, participants should seek assistance from local emergency services as appropriate.

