**Specific clinical AN related risk**

One study of psilocybin 25mg for adults with AN, reported no clinically significant changes in ECG, vital signs, or suicidality levels (Peck et al., 2023). Only two participants experienced asymptomatic hypoglycemia post-treatment, which resolved within 24 hours. Additionally, no significant changes were noted in laboratory values. All adverse events (AEs) observed were mild and temporary. The overall participant feedback indicated that the treatment was generally well-received and deemed acceptable.

To mitigate potential risks, participants in this study will undergo comprehensive medical screening, including blood tests and ECG, before dosing session. A trained physician will be present during all psilocybin sessions to address medical emergencies, if needed.

4. Trial Objectives

For full list of measurements, please see attachments.

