7.1 Description of Investigational Medicinal Products

Psilocybin: 25 mg, administered orally in a controlled clinical setting with manual based psychological support. The time for dosing is 10am and the duration of the dosing session is approximately 6-8 hours.

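### Section 5.2 gives two contradictory rules on whether a participant who deteriorates between visits may contact the research team out of hours

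*Protocol*

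**What the plan says.** **Contact between visits.** Two paragraphs of Protocol Section 5.2 deal with this.

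- Under *Extended Follow-Up Phase*, after the list of 12-month assessments, a closing paragraph names the group concerned as "Participants who show signs of psychological or physical deterioration at any point during the study between follow-ups". Its instruction to this group is that they "are instructed to contact the research team at any time and will be offered additional assessment and support".
- Under *Monitoring Post-Psilocybin Administration adverse events between visits*, participants with marked distress, deranged vital signs or another health problem "are instructed to contact the research team during daytime hours using the contact details provided in the participant information sheet". The next sentence reads: "During evenings or weekends, participants should seek assistance from local emergency services as appropriate".

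**Timing of dosing.** Section 7.1: "The time for dosing is 10am and the duration of the dosing session is approximately 6-8 hours".

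**Physician cover at dosing.** Section 3, *Specific clinical AN related risk*: "A trained physician will be present during all psilocybin sessions to address medical emergencies, if needed". Section 5.2, *Description of Psilocybin Administration and Psychological support*: "During the dosing session, a medically trained study doctor will be available, equipped for emergencies". That part of Section 5.2 also mentions a psychiatrist who is both on site and on call during the session.

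**How events reach the team.** Section 4.3 makes AE and SAE incidence the primary endpoint. Section 8.2 has AEs reported spontaneously, by participant or clinician, at in-person visits from first dosing. Section 9.3 has clinicians record them at each contact with a participant, and starts the 24-hour SAE report when the investigator becomes aware.

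**The concern.** Both contact paragraphs are current operative text, and both describe what participants are told to do. One sets no limit of hour. The other limits contact to daytime and names a different service for the rest of the week. A participant who becomes unwell on a Saturday, or on the evening after a dose, gets a different answer depending on which paragraph the information sheet follows. Staff and monitors likewise have no single standard to check against.

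Two things are at stake. The first is safety: the population is vulnerable, includes 16- and 17-year-olds, and is being dosed with a drug for which Section 3 itself lists acute psychological reactions and suicidality as risks. The second is ascertainment of the primary endpoint. The reporting clock runs from the investigator's awareness, so whether an out-of-hours event goes to the team or to an outside service affects how soon the clock starts.

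**Working it through.** The plan gives no figure to reproduce, and the point rests on no error rate, power or sample size. The check is a comparison of texts plus one piece of clock arithmetic.

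**Step 1. The two contact rules side by side (both in Section 5.2).**

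| | *Extended Follow-Up Phase* | *Monitoring Post-Psilocybin Administration…* |
|---|---|---|
| Who | Participants deteriorating psychologically or physically | Participants with distress, deranged vital signs or other health problems |
| When it applies | Any point in the study, between follow-ups | Between study visits |
| Daytime on weekdays | Research team | Research team |
| Evenings and weekends | Research team | Local emergency services |
| What is offered | Additional assessment and support | Not stated |

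The groups overlap: deterioration of the kind in the first column is a health concern of the kind in the second. The periods overlap too, because every interval between follow-up visits is an interval between study visits. The rules agree in the daytime and conflict on evenings and weekends.

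**Step 2. Does the first evening after dosing fall in the conflict?** Inputs are from Section 7.1.

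- Earliest end of session: 10:00 + 6 h = 16:00.
- Latest end of session: 10:00 + 8 h = 18:00.

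The evening begins at or soon after the end of the session, and the next scheduled contact is the integration session the following day. The first evening and night are therefore out of hours under the daytime rule. With 20 dosed participants (Sections 5.1 and 10.1) and one or two doses each, this arises 20 × 1 = 20 to 20 × 2 = 40 times in the randomised active arm, before any later switch by controls.

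**Step 3. How long could an event stay unknown to the team?** If an out-of-hours event is handled elsewhere and nobody contacts the team, it surfaces at the next visit. From the Section 5.2 schedule:

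- after a dose: the next day;
- week 5 to week 9: 9 − 5 = 4 weeks;
- month 6 to 9, and month 9 to 12: 3 months each.

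These are upper limits on delay, not expected delays.

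**Step 4. Physician cover.** Section 3 says a physician is present. Section 5.2 says a study doctor is available and equipped for emergencies, and puts a psychiatrist on site and on call. A doctor on the premises at every session satisfies both texts, so the terms differ without strictly contradicting each other. Section 5.2 does not say whether the study doctor and the psychiatrist are one person or two.

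**The case against.** **The two contact rules might apply to different phases.** One sits under the extended follow-up heading and the other under a post-dosing heading. This does not work: the first states that it covers any point in the study, and the second covers the gaps between all visits. If a reader nevertheless confines the first rule to the gaps between the later follow-up visits, the first-evening example weakens, but the rules still collide throughout those gaps.

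**Events are captured by other routes.** This largely stands. Section 9.3 records AEs at each contact, Section 8.1 takes hospitalisations from patient reports confirmed in medical records, and Section 5.2 draws rehospitalisation and added interventions from patient registers. The day after each dose there is a visit with suicidality and psychiatric ratings, ECG, vital signs and blood tests. A reader might infer that an out-of-hours event has no path back to the team; the protocol does not support that. What remains is that these routes depend on spontaneous report or on later retrieval with no stated timing.

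**Hypoglycaemia in the earlier anorexia study might be cited as an event that out-of-hours contact would catch.** It should not be. Section 3 describes it as asymptomatic, so it would prompt no call, and glucose is measured the next day.

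**The benefit-risk case might be said to rest on cover that will not be provided.** The documents do not show this. Section 3 states no contact hours, so the contact conflict contradicts nothing there. The physician wording is compatible with a doctor on the premises. There is also only one clinical site, so divergent practice between sites does not arise.

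**Conclusion.** The contradiction on out-of-hours contact is established from the text alone and needs no assumption. It is an internal inconsistency that should be corrected because of its bearing on safety and on prompt awareness of primary-endpoint events. It does not alter an endpoint definition, the sample size or any planned analysis.

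Its practical reach is 20 to 40 first evenings in the active arm, on the reading that the first rule covers the whole study, plus every evening and weekend between later visits on either reading. The session end times assume dosing at the stated hour and the stated duration; no discharge time is given.

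A reader might want to express the conflict as a share of the week covered. The protocol does not define daytime hours, so any such percentage would measure an assumed office timetable and is best left out.

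The difference in wording on physician cover is minor: the terms should match, but a reader who infers that a lesser level of cover will be given goes beyond what the passages say.

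**What to change.** 1. Reconcile the two Section 5.2 paragraphs into one contact rule covering all hours. Which arrangement to adopt is for the sponsor and investigator. Give the rule once and refer to it from the other place.
2. Match the participant information sheet to that rule.
3. Whichever rule is kept, add a standard question at the existing visits, from the day after first dosing onwards: has the participant had any out-of-hours contact with emergency services since the last visit? Record the answer so that it feeds the AE log and, where applicable, the SAE report.
4. As a wording alignment, describe physician cover at dosing in the same terms in Section 3 and Section 5.2, and say whether the study doctor and the psychiatrist are the same person.

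The cost is an edit to the protocol and the information sheet, and one extra question per visit. No new visit, sample or analysis is needed.
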